### Data monitoring and quality control

The project assistant, who has a master’s degree in sports coaching and management and is a certified fitness coach, has solid experience delivering exercise classes to older people. He coordinates with the instructors, participants, social workers of the community centres and the other trained assistants. The instructor has a master’s degree in physical education and is a certified fitness instructor. He has over ten years of experience delivering exercise classes to older people and people with chronic diseases. Additionally, he already had one year of experience teaching exercise classes online before our study had started. The five trained assistants who will be blinded to the group assignment will perform assessments with the participants. The other ten trained assistants and the project assistant will arrange home visits for the participants of the TE group and set up the mobile device for the Zoom class. A family doctor with Specialist qualification in Community Medicine, an occupational therapist and an exercise physiologist will oversee the medical clearance and safety of the participants. The principal investigator and the project assistant will be responsible for monitoring the study and overseeing all the procedures.

### Data management and dissemination

Data will be collected by the outcome assessors using the tailored report forms. The project assistant will input the data into the computer and ensure their integrity and accuracy. The study protocol can be obtained through the Chinese Clinical Trial Registry Website (https://www.chictr.org.cn/hvshowprojectEN.html?id=219002&v=1.1) under registration number: ChiCTR2200063370 (Registered on 5 September 2022). The results of this study will be disseminated at an international conference, and by publications in high-impact peer-reviewed journals. The datasets generated during the current study will be available from the corresponding author upon reasonable request.

## Discussion

This study evaluates whether the tele-exercise approach is comparable to a traditional face-to-face exercise class in terms of physical functioning and exercise adherence during the 3-month intervention and the subsequent 9-month maintenance phase among the older people with possible sarcopenia or at risk of falls. Traditional face-to-face exercise classes allow the instructor to monitor older people’s performance and promote social interaction. However, the time and space available for such group classes for older people are limited. Frail older people may have less confidence to leave their home to attend classes in the community [8]. They may need support from their family. The transportation arrangements may also affect how likely they will participate in the programme. The recent social distancing policy during the COVID-19 pandemic has also been a crucial factor resulting in the frail older people baulking from participation in exercise programmes in the community. Consequently, health professionals are also urging governments to prepare for the next pandemic [46]. Considering older people are more willing to do strength and balance training at home [47], a feasible and effective alternative should be offered to them. The tele-exercise approach in this study uses an online communication application, Zoom, to deliver live group exercise classes in their home. It is convenient in that this approach avoids commuting time and older people can attend classes even in bad weather and could also do so during the pandemic. Frail older people can exercise with others at the same time with less social consciousness and peer pressure [48]. The strength of the current study is that we consider the needs of older people to interact and their fear of new technology. Each lesson will be well structured with a short break every 10 min to allow interaction in both groups. The team will arrange a home visit to the TE group before the intervention period and guide the setting up of the tablet and their home environment such as the angle of the tablet stand, where the tablet and chair should be positioned and where the participant should stand. During the lessons, our team will control the tablet of each participant remotely to minimize any technological problems that they may encounter.

Regular physical activities are well-known to have benefits in regard to balance, muscular strength and functional mobility particularly for older people. The benefits depend on the adherence to their exercise regimen and the satisfaction that they derive from it. Older people with a higher perceived risk of falling are associated with poorer exercise adherence and their adherence to exercise interventions decreases over time [49]. The main barriers include environmental constraints, resources (cost and aversion to gyms), behavioural regulation (motivation) and emotion (boredom) [50]. In other words, if older people are motivated and encouraged continuously, they can exercise in an environment in which they feel comfortable, and if the exercise programme is interesting without much cost, older people are more likely to maintain their exercise habit. The current study aims to address the physical functioning of older people and their experience with an exercise programme. Therefore, strategies to enhance their exercise experience are emphasized based on the findings of previous studies as described under the “Methods” section. The areas we will focus on are namely self-efficacy, self-confidence, and empowerment [17, 49]. The instructor and the speakers for health talks will also be older indivduals who will serve as a role model to enhance the confidence of the participants in maintaining regular exercising habits and adopting a healthier lifestyle. The modified Otago exercise programme is adopted in this study as it has been shown to be an effective home tailored exercise programme to prevent falls among older people [24]. The problems of lack of engagement and interesting variations of movements of the original OEP will also be addressed. The lesson plan will emphasize interaction by allowing short breaks between sessions. The instructor and the project assistant will approach the participants to elicit their comments. The last session of each lesson will be “Workouts on-demand”. Additional exercises such as those focused on mobility, flexibility and strength training for various body parts will be introduced based on the comments of the participants in addition to the OEP.

The major concern of the research team is the safety of the older people at risk of falls while exercising at home alone. All the participants will have met the inclusion criteria and pass the preparticipation Health Screening of the American College of Sports Medicine (ACSM). Potential participants diagnosed with dementia or cognitive impairment and severe vision impairments will be excluded from the study. We have a strong team to uphold the safety of the programme. A family doctor is responsible for the medical clearance of the participants. The instructor and the project assistant are experienced in delivering exercise classes to older people. They have familiarized themselves with the safety protocol and understand when to call for emergency help. The OEP adopted in the current study is well-known for its safety. Even for unsupervised home-based OEP, two studies showed that none of the participants who were older fallers with a mean age ranging from 76.2 to 81.4 years reported any symptoms or adverse events associated with the exercises [51, 52]. In another study [53], two participants reported lower back pain associated with the exercises. One resumed exercising and the other discontinued the exercises. The rate of adverse events associated with the OEP is relatively low. A systematic review conducted by Mañas et al. [54] evaluated the safety issues of unsupervised home-based resistance training for community-dwelling older adults in 21 studies and reported no major adverse events. It was also found that the incidence of adverse events was similar between the training intervention group and the control groups, suggesting that unsupervised home-based resistance training is safe [54].

The study has three main limitations. Firstly, due to budget constraints, we can only lend equipment to participants of TE during the intervention period. Online exercise courses offered by the local course providers commonly require participants to have their own devices and Wi-Fi connection, with minimal technical support provided. Participants who borrowed tablets and sim cards from us may not be able to continue their exercise online during the maintenance phase. Instead, we suggest that all participants, including both TE and CB, aim to achieve 10,000 steps daily. They should also follow the guidelines in our exercise booklet and exercise videos, which outlines our exercise programme for practicing at home. Furthermore, we encourage participants to take advantage of exercise courses available in their district. Secondly, as travel restrictions are relaxed after the COVID-19 pandemic, some participants may plan to stay outside of Hong Kong for an extended period, which could impact their ability to maintain their activity level during the maintenance phase. Thirdly, the administration of a large number of tests at different time points may increase the dropout rate and lead to missing data. Therefore, it is important to pay greater attention to these areas and implement strategies to minimize these problems. Possible strategies could include regular phone calls and text messages to the participants, well-trained outcome assessors and regular monitoring of the data collection procedures by the project assistant.

This paper presents the design of a clinical trial to examine the possibility of a tele-exercise approach for the older people with possible sarcopenia or at risk of falls. The intervention of the current study includes 3 months of supervised exercise delivered either online (TE) or face to face (CB) which helps the participants to gain confidence to build up their exercise habits during the subsequent maintenance phase. The team has focused intensively on the different strategies to enhance the exercise experience of the participants and their safety. The comprehensive assessments of the study can help to propose an exercise delivery and maintenance model for future practices.

### Trial Status

Protocol version number: 1.1.

Date of recruitment began: September 2022.

Recruitment will be completed when 92 participants are enrolled.

Current status: 2 groups of CB completed 3 month intervention. 1 group of CB and 2 groups of TE are in the intervention phase. We will recruit 5 more groups to meet the target.

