### Randomization and blinding

After the screening phase, ten community centres will be coded and then randomized such that a similar number of centres will be allocated to either the tele-exercise group (TE) or community-based group (CB) in a concealed, blinded fashion to minimize cross-over contamination between the groups. An independent assistant will oversee the randomization procedures and allocation sequence. Around ten participants will be recruited from each centre. The assessments will be performed by trained outcome assessors who will be blinded to the group assignments. It is impossible to blind the participants in the training mode. However, they cannot communicate with other groups of participants because they are recruited from different locations. The instructors and researchers will not be blinded and will be asked to refrain from discussing the group assignments of the participants with the outcome assessors.

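### Starts are staggered and the first completed wave is CB only; allocation balances the number of centres per arm but not their start time, so a partial calendar imbalance between arms is a risk worth limiting

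*Protocol article*

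**What the plan says.** The unit of allocation is the community centre. Randomization and blinding says that "ten community centres will be coded and then randomized such that a similar number of centres will be allocated to either the tele-exercise group (TE". The CB arm takes the other centres, with about ten participants per centre. The section describes no pairing or blocking of centres by start date.

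Trial Status shows that the groups do not start together: "Current status: 2 groups of CB completed 3 month intervention. 1 group of CB and 2 groups of TE are in the intervention phase". On the rest of the trial, the same section adds: "We will recruit 5 more groups to meet the target". Recruitment began in September 2022. No start date is given for any group, and the arms of the last five groups are not stated.

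Statistical analysis names a two-way repeated measures ANOVA with group and the group-by-time interaction. Time there means the study visit (baseline, months 3, 6 and 12), not the calendar.

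The Discussion treats outside circumstances as relevant to taking part. It names social distancing as an important reason why frail older people stayed away from community programmes. It describes online delivery as a setting where "older people can attend classes even in bad weather and could also do so during the pandemic". It lists as a limitation that "as travel restrictions are relaxed after the COVID-19 pandemic, some participants may plan to stay outside of Hong Kong for an extended period", with a possible effect on activity in the maintenance phase.

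**The concern.** Balancing how many centres each arm receives does not balance when they run. With only ten units and staggered starts, one arm can by chance hold more of the early places, and so far this has happened: the earliest wave contains CB groups only. Because every group keeps the same visit schedule, a start offset carries through to the 3-, 6- and 12-month assessments.

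The outcomes most exposed are attendance, dropout, and exercise maintenance (PASE, diary, accelerometer). By the protocol's own account, restrictions and travel influence participation and activity, and adherence belongs to the first study purpose. If conditions changed between the first wave and the later ones, part of a TE–CB difference, or part of its absence, could reflect when the groups ran rather than how the classes were delivered. Concealed allocation would not prevent this.

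**Working it through.** **Inputs.** Trial Status: completed 2 CB and 0 TE; running 1 CB and 2 TE; still to recruit 5. Randomization and blinding: ten centres, a similar number per arm. Interventions: 3 months for every group, in classes of 9–10. Assumption: the final split is exactly 5:5.

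**1. Group count.** 2 + (1 + 2) + 5 = 10, which agrees with the ten centres. At 5:5 the last five groups are 5 − 3 = 2 CB and 5 − 2 = 3 TE.

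**2. Order of starts.** The programme length is common, so a completed group started before a running one. This gives three waves: 2 CB:0 TE, 1 CB:2 TE, and (assumed) 2 CB:3 TE. It fixes the order, not the time between waves.

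**3. Is this compatible with chance?** The probability that the first two of ten centres are both CB is 5/10 × 4/9 = 0.22; both in the same arm, 0.44. Mean wave is (1+1+2+3+3)/5 = 2.0 for CB and (2+2+3+3+3)/5 = 2.6 for TE. Of the 252 possible 5:5 allocations, 44% give a difference in mean wave at least this large in either direction. So the pattern is ordinary under randomization. For the same reason, randomizing ten centres cannot be relied on to balance start time.

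**4. How strongly are arm and wave tied?** The CB share by wave is 1, 1/3 and 2/5.
- Between-wave sum of squares: 2(0.5)² + 3(1/3 − 1/2)² + 5(0.4 − 0.5)² = 0.500 + 0.083 + 0.050 = 0.633.
- Total: 10 × 0.25 = 2.5.
- R² = 0.633/2.5 = 0.25, and variance inflation = 1/(1 − 0.2533) = 1.34, or √1.34 = 1.16 on the standard error.

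Arm and wave are associated but separable.

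**5. What the remaining five can change.** Suppose the groups within each wave also start one after another. Over all orders consistent with Trial Status, the correlation of arm (CB = 1) with start order then runs from −0.59 to −0.03. The scheduling of the last five therefore matters.

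**6. Illustration of size.** Suppose the first wave differs from all later ones by a period effect δ and later waves share one level. The shift in the CB-minus-TE mean is then (2/5 − 0/5) × δ = 0.4δ. The documents give no δ. An assumed 5 to 20 percentage points on attendance would give 2 to 8 points. With 6 or 4 CB centres instead of 5, the multiplier is 2/6 = 0.33 or 2/4 = 0.50. The two early CB groups hold about 18–20 people.

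**The case against.** A reader might infer more: that delivery mode is confounded with season or with the lifting of COVID-19 restrictions, or that CB starts early and TE late as a matter of design. The documents do not support either reading.

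- The only date is the start of recruitment. Neither group start dates nor policy dates are given, so the completed CB groups may have led the running TE groups by only a short time.
- Trial Status is a progress report at the halfway point, not a rule on start order. The pattern has probability 0.22 under random 5:5 allocation.
- One CB and two TE groups run concurrently, and the arms of the last five are unstated. Near-zero imbalance in start order is still possible.
- Attendance that does not depend on weather is part of what online delivery offers. It would distort the comparison only if the arms met different weather, which is not shown.
- The travel limitation concerns some participants in the maintenance phase and is not linked to arm.
- The period effects used for illustration are assumptions.
- A condensed article may leave a start-period term to a full analysis plan, so its absence is not in itself a fault.

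All of this stands, and it limits the point to a risk of partial imbalance. It does not remove it. The earliest wave is CB only, no later scheduling at 5:5 can put a TE group into it, and the stated allocation does nothing to prevent further drift. Start order is also a matter of conduct, which an analysis plan cannot arrange.

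**Conclusion.** The point holds as a risk, not as a demonstrated bias. What the document establishes is staggered starts, a first wave of 2 CB and 0 TE, and an allocation that balances numbers of centres but not start times. Under an assumed 5:5 split, wave explains about a quarter of the variation in arm. Any first-wave period effect would enter the arm comparison at about 0.4 of its size, provided that later waves share a common level.

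Whether such an effect exists, and whether it follows season or policy, cannot be settled from the article. The physical function measures are less directly tied to calendar conditions in the text than adherence, dropout and maintenance. This is a cheap improvement that was still open while half the groups had not been recruited.

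**What to change.** **Recruitment; Randomization and blinding.** Keep the randomized allocation of centres. Start the five remaining groups concurrently across arms where possible: TE/CB pairs beginning in the same month, with the odd group alongside one of the pairs. Three groups across both arms already run at the same time, so this is feasible. It cannot repair the first wave, but it prevents the imbalance from growing.

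**Statistical analysis.** Add a sensitivity analysis that keeps all randomized participants and adjusts for start wave. A comparison restricted to concurrently started groups can be supportive only. It leaves out two of an assumed five CB centres, departs from the planned intention-to-treat set, and would be chosen after the start sequence is known.

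**Reporting.** Give the start month of each group by arm, so that readers can judge the overlap.

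**Cost.** A centre in a pair may wait a few weeks; no extra participants or staff are needed. The adjusted estimate is less precise: variance inflation is about 1.34 at 5:5. Two wave terms also take two of the centre-level degrees of freedom (10 − 2 = 8 without them, 10 − 4 = 6 with them). That is why the adjustment belongs in a sensitivity analysis.

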## Data Availability

Data sharing is not applicable to this article as no datasets were generated or analysed during the current study.
